### Analysis of the secondary outcomes

Continuous data will be summarised descriptively, and also with a general linear model, and adjusted for patient age and sex. Dichotomous data will be summarised descriptively and will analysed using a logistic regression adjusted for: patient age and sex.

We note that many data will be gathered relating to the questionnaire itself. This useful clinical data warrants publication in its own right; however, it is not the focus of this study and will form a separate stand-alone analysis.

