### Study setting

The study will be undertaken in 14 centres across England and Wales. Centres acting as research sites will be those who were previously involved in potentially eligible participants’ post stroke care. In line with the time-frame of the study, the majority of potentially eligible participants will reside in the community and will be anticipating routine clinical follow-up from the centres acting as research sites.

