	Modified Rankin Score on discharge or transfer from stroke unit: 0–6
	Clinically confirmed diagnosis of aphasia as sequela of ICD I63, I61 or I64?: (data collected at 3 sites within a single Health Board only) Yes / No

All demographic data and routinely collected clinical data will be stored against a Participant Research Number in the research data base. Personally identifiable information will only be stored at the research sites and will not be stored for those who do not offer informed their consent before the cut-off period of 4 weeks following the posting of the second letter Therefore, no personally identifiable information will be held by the central research team.

All consented participants will receive the PRHSQs. The PI at site as a member of both the research team and the participant’s own care team will be responsible for arranging or delegating the completion of the questionnaires between 4 and 8 months post stroke. There are schema for each method by which the PI must abide; however, the methodologies for all four methods of administration differ slightly and are as follows:

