#### Secondary outcomes

The proportion of individuals eligible for the study who return the method specific PRHSQs in each of the four study arms (postal, online, face-to-face and telephone) for individuals with communication issues (i.e. aphasia)The proportion of individuals eligible for the study who return the method specific PRHSQs in each of the four study arms (postal, online, face-to-face and telephone) by stroke severity as defined by individual NIHSS on admissionThe proportion of individuals eligible for the study who return the method-specific PRHSQs in each of the four study arms (postal, online, face-to-face and telephone) by stroke type; Cerebral Infarct (ICD I63), Cerebrovascular Haemorrhage (ICD 161) or Stroke, not specified as haemorrhage or infarction (ICD I64)

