### Statistical analysis

#### Analysis of the primary outcome

We will carry out a difference of two proportions between the three intervention groups (postal, telephone or online) verses face-to-face administration, with a 2.5% non-inferiority margin. The three comparisons will be adjusted using a Holm [24] multiplicity adjustment, with a two-sided alpha = 0.05. The analysis will be presented as a difference with an associated 95% confidence interval (CI).

Analyst and researchers blinding to the allocation will remain in place until interpretation of the primary and secondary outcomes are agreed. Following un-blinding of the allocation, difference will be generated in the three comparator allocation groups, and face-to-face completion rate, and will include the non-inferiority margin of 2.5%, as our primary analysis.

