#### Secondary analysis of the primary outcome

We plan to repeat the primary analysis after adjustment for: age; sex; National Institutes of Health Stroke Score (NIHSS) on admission and stroke type (Haemorrhagic or Ischaemic).

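### The logistic model adjusted for age and sex is not matched to secondary outcomes defined as return by arm according to NIHSS and stroke type, and it leaves out centre

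*Protocol article*

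**What the plan says.** The Secondary outcomes section of the protocol article lists three outcomes. Each is the proportion of eligible people who return the questionnaire in each of the four arms. The first is restricted: "for individuals with communication issues (i.e. aphasia". The second is broken down by admission NIHSS. The third is given "by stroke type; Cerebral Infarct (ICD I63", with I61 and I64 as the other two categories.

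Under Analysis of the secondary outcomes, the rule for such data is: "Dichotomous data will be summarised descriptively and will analysed using a logistic regression adjusted for: patient age and sex". The same paragraph gives a general linear model for continuous data, although none of the three listed outcomes is continuous.

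For the primary outcome the effect measure is explicit: "We will carry out a difference of two proportions between the three intervention groups (postal, telephone or online) verses face-to-face administration", and "The analysis will be presented as a difference with an associated 95% confidence interval (CI". NIHSS and stroke type enter a model only where the primary comparison is rerun with covariates: "We plan to repeat the primary analysis after adjustment for: age; sex; National Institutes of Health Stroke Score (NIHSS) on admission and stroke type", with type there coded in two classes, not three.

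Three design facts bear on this. The Randomisation section stratifies permuted blocks by centre. Study setting states: "The study will be undertaken in 14 centres across England and Wales". Table 1 says of the aphasia item: "data collected at 3 sites within a single Health Board only". The Sample size section warns that secondary outcomes may be unpowered.

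**The concern.** The characteristics that define the secondary outcomes do not appear in the model given for them, and no section links the two. Applied to all randomised people with arm, age and sex, the regression would return one overall contrast per mode. That repeats the primary comparison with a different adjustment set and says nothing specific about severity or stroke type.

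The trial has an evident interest in that question. The Discussion expects to relate demographic and clinical features to uptake of each allocated method, although it speaks there of consent and not of return. The Non-inferiority margin section suggests that disability and communication problems may partly explain the preference for face-to-face review. What is at stake is whether the inferential part of the secondary analysis can inform a service that wants to know for whom a remote mode loses returns.

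Centre is a separate gap. It is the only stratification factor in the randomisation, and the Discussion itself expects organisational differences between sites, yet the model does not include it.

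**Working it through.** The article states no figure on this point, so there is none to reproduce. The first step sets the sections side by side; the rest is illustration.

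**1. Outcome against model**

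- Aphasia: a comparison of arms within one group. It needs no interaction term, and descriptive proportions answer it.
- NIHSS: return by arm across severity. NIHSS is not named in the model, nor is an arm-by-NIHSS term.
- Stroke type: return by arm across three codes. The same gap applies.
- Centre: the randomisation stratum, not named in the model.

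Adding NIHSS or stroke type as a main effect would not close the gap. A main-effects logistic model holds the odds ratio for mode constant across levels, so it assumes the answer to the question.

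**2. Why the scale matters**

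Inputs: face-to-face return p0 = 85% (Non-inferiority margin section). The other rates and the 10-point deficit are assumptions.

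OR = [p1/(1 − p1)] / [p0/(1 − p0)], with p1 = p0 − 0.10:

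- p0 = 0.90: (0.80/0.20)/(0.90/0.10) = 0.44
- p0 = 0.85: (0.75/0.25)/(0.85/0.15) = 0.53
- p0 = 0.70: (0.60/0.40)/(0.70/0.30) = 0.64
- p0 = 0.50: (0.40/0.60)/(0.50/0.50) = 0.67

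Conversely, hold OR = 0.529 and compute p1 = o/(1 + o), where o = 0.529 × p0/(1 − p0):

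- p0 = 0.90: p1 = 0.827, difference −7.3 points
- p0 = 0.85: p1 = 0.750, difference −10.0 points
- p0 = 0.70: p1 = 0.553, difference −14.7 points
- p0 = 0.50: p1 = 0.346, difference −15.4 points

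So a constant effect on one scale varies on the other. Risk differences standardised from a model without an interaction would vary with severity partly because of the model's form.

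**3. How precise an interaction estimate would be**

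Inputs: 202 per arm (Sample size section, taken only as the planned size); a binary characteristic with share f (assumed); common return rate p; two-sided 5% level and 80% power, so the multiplier is 2.8016.

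SE = √{2p(1 − p)[1/(202f) + 1/(202(1 − f))]}; detectable difference between two risk differences = 2.8016 × SE.

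- p = 0.85, f = 0.5: √[0.255 × (1/101 + 1/101)] = 0.0711, giving 20 points
- p = 0.85, f = 0.1: √[0.255 × (1/20.2 + 1/181.8)] = 0.1184, giving 33 points
- p = 0.50, f = 0.5: 28 points
- p = 0.50, f = 0.1: 46 points

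These estimates would be imprecise, which supports an exploratory label.

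**4. Aphasia**

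Assumptions: even recruitment over 14 sites, 20–40% with aphasia, return near 50%.

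- 808 × 3/14 = 173 people at the three sites
- 173 × 0.20 to 0.40 = 35 to 69 with aphasia; divided by 4, about 9 to 17 per arm
- 95% half-width for a difference = 1.96 × √(2 × 0.25/n), about 47 points at the low end and 33 at the high end

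Description with confidence intervals is all that these numbers would support.

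**The case against.** The article is a condensed account and refers to a statistical analysis plan that is not shown; model terms are often settled there. The adjustment list names covariates, not every term: arm is not named either, and nobody would infer that it is left out. The promised descriptive summaries already give the proportions that the outcomes literally define. No hypothesis that the mode effect differs is stated, and the lack of power is disclosed. The remedy buys little precision, and three stroke codes crossed with four arms may give sparse cells.

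Most of this stands, and it lowers the severity. It does not remove the point. The article chooses an inferential model and an adjustment set, that choice does not fit the NIHSS and stroke-type outcomes, and a better-matched model is available at little cost.

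A reader might go further in four ways that the document does not support:

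- That the trial will report odds ratios. No effect measure is named for the secondary outcomes, and logistic output can be standardised to proportions and differences.
- That significance in one subgroup will be set against non-significance in another. No section plans this.
- That results by subgroup will be judged against the 2.5-point margin. The margin is applied to the primary outcome only.
- That return will differ strongly by severity or aphasia. The article says only that disability and communication issues may influence the choice of face-to-face review.

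**Conclusion.** The concern holds in a limited form. The inferential model for the secondary outcomes is not matched to return by arm according to NIHSS and stroke type. As a main-effects model it would not show whether the mode effect differs by these characteristics, and it omits the randomisation stratum. The descriptive proportions are sound and should stay, and the aphasia outcome needs no interaction term.

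Severity is low: the outcomes are secondary and not claimed to be powered, and the primary comparison is untouched. The mismatch and the omission of centre rest on the text alone. The sizes rest on assumed return rates other than 85%, assumed subgroup shares, even recruitment across sites and an assumed aphasia prevalence; they illustrate the issue and do not forecast results.

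**What to change.** Keep the descriptive proportions per arm and subgroup. Replace the regression sentence along these lines: for NIHSS and for stroke type, one binomial model each will be fitted over all randomised people, with arm, the characteristic, arm-by-characteristic, age, sex and centre. Standardised return proportions per arm and risk differences against face-to-face will be reported across levels of the characteristic, with confidence intervals for how those differences vary.

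This puts the secondary results on the same scale as the primary analysis. Also:

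- State that these analyses are exploratory and that no non-inferiority claim will be made within subgroups.
- Report aphasia descriptively, with confidence intervals, for the three sites that record it.
- Reconcile the stroke-type coding, which has three categories in the outcome definition and two in the adjusted primary analysis.

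The cost is revised wording and a little more analysis, with no change to trial conduct. The interaction estimates will be imprecise, especially for uncommon stroke types, and should be reported as such.

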### Missing data and analysis population

We will be reporting using a complete case analysis. Due to the nature of the research question, we are expecting missing data, and anticipate that this will be not missing at random. We will describe patterns of missing data. However, the primary objective of this study is to ascertain if the missing data is systematically more likely in the comparator groups, compared to the face-to-face allocation group.

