### Data management

Data will be collected at the research sites until February 2018. Potentially eligible participants who do not respond or consent will not be excluded from data analysis of their demographic and routinely collected non-identifiable clinical data as this data is essential for the determination of acceptability of the methods under investigation. However, individuals who do not consent will not receive the PRHSQs.

Two levels of data management exist for this research study. The first level is that of the individual research site which will have access to identifiable patient data. This will allow the site to invite potentially eligible participants and to contact participants who consent to receive the PRHSQs via the method randomly assigned. Following completion of the PRHSQs the anonymous data received from the two self-administered questionnaires (postal or online) will be populated in the research data base against the corresponding Participant Research Number as detailed on the returned PRHSQs. The data from the two administered methods (face-to-face or telephone) will be captured via anonymised PRHSQs, identified solely by the Participant Research Number.. Data is to be initially coded and entered into a site level data base. The data base has been developed using Microsoft Excel 2013 to support ‘data validation’ and will not accept any data entered outside pre-defined ranges for each discrete data value to be collected. Additionally, ‘conditional formatting’ will be utilised to ensure that double entry is minimised..

The second level of data management is that of the central research team. No personally identifiable information will be transferred or held in the central research data base. Research sites will transfer data to the research team using the Participant Research Number as the unique discriminator. Data quality will be ensured by the trial statistician ([name], Senior Lecturer in Biostatistics, King’s College London) by conducting central data verification prior to data base lock. Data queries arising from data verification procedures will be submitted to sites in writing and sites will have two working weeks to respond in full.

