### Outcomes

#### Primary outcome

The proportion of individuals eligible for the study who return the method specific PRHSQs in each of the four study arms (postal, online, face-to-face and telephone)

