## Discussion

This pragmatic randomised controlled trial will provide insight into the optimal method of PROM delivery in stroke survivors and also inform the choice of delivery method across other chronic disease conditions, especially conditions associated with chronic physical disability. The choice of a pragmatic study design, whilst offering good generalisability and the testing of a hypothesis under as near to ‘real-world’ conditions as is possible, can and will offer substantial challenges. The ‘natural’ organisational variances of each research site, require careful and thorough discussions to ensure that research is not disruptive to routine clinical work and that the research procedures outlined within the protocol are adhered to.

We assume a possibility that the pragmatic design of the research study will not be accessible to all individuals post stoke. Nevertheless, all eligible individuals are to be accounted for in data analysis. It is believed, that this will offer possible correlations as to why certain demographic and clinical features relate to the number of consented participants for each allocated method.

The benefits of this study, to stroke survivors is in the fact that they will offer clinicians and healthcare commissioners early evidence as to which method they find most acceptable, when compared against the most commonly commissioned approach. Moreover, due to the assumption that data is missing not at random, those who do not respond offer useful data. Therefore, any actions taken on the basis of the final analysis of this study can do so in the knowledge that those actions are based on the preferences of all the eligible stroke survivors approached for the study.

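### The analysis-population section prescribes an unscoped complete-case analysis while using missing data to mean non-return, which is the primary outcome; this contradicts the plan's own denominator of all eligible people

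*Protocol article*

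**What the plan says.** The section of the protocol article headed Missing data and analysis population opens with "We will be reporting using a complete case analysis". It continues that "we are expecting missing data, and anticipate that this will be not missing at random", and ends by saying that "the primary objective of this study is to ascertain if the missing data is systematically more likely in the comparator groups" than in the face-to-face group. The rule is not restricted to covariates, to questionnaire items or to secondary models.

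Other sections describe a different population:

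- **Primary outcome:** "The proportion of individuals eligible for the study who return the method specific PRHSQs in each of the four study arms".
- **Sample size:** 808 randomised eligible participants, 202 per arm, are stated as the minimum for the statistical analysis.
- **Discussion:** "all eligible individuals are to be accounted for in data analysis", and readers may act on the results knowing that "those actions are based on the preferences of all the eligible stroke survivors approached for the study".
- **Data management:** "Potentially eligible participants who do not respond or consent will not be excluded from data analysis of their demographic and routinely collected" clinical data, but "individuals who do not consent will not receive the PRHSQs".

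Under Study design and Trial procedure, consent is sought by post after randomisation, for the allocated mode only.

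**The concern.** For an outcome of returned or not returned, a person who sends nothing back has an observed result: not returned. Calling that result missing and then prescribing complete cases invites an analyst to remove the failures that the trial exists to count. The paragraph itself expects these data to be not missing at random, which is where complete-case analysis is hardest to defend.

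The design adds to the problem. People who do not consent never receive the questionnaire, and they decide knowing which mode they have been offered. Refusal is therefore part of how acceptable that mode is. A set restricted to returners or to consenters is selected by something that happened after randomisation and may depend on the arm. What is at stake is the primary denominator, and with it the meaning of all three non-inferiority comparisons.

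**Working it through.** The plan gives no figure for the effect of this rule. The check first compares the sections and then applies each candidate denominator to assumed rates.

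**1. Comparing the sections.** The Primary outcome denominator is eligible individuals, and Sample size and Discussion agree with it. In the analysis-population section the missing quantity, whose frequency by arm is the primary objective, can only be non-return. A case complete on that quantity is a returner. An eligible non-returner is thus a failure in one section and not a case in the other. Data management does not settle this, because it keeps non-consenters only for their demographic and routine clinical data. No section of the article states that non-return is coded as failure.

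**2. Returners-only denominator.** Inputs: 202 per arm (Sample size); face-to-face about 85% (Non-inferiority margin, where it describes follow-up attendance, so it is an assumption here); comparator 70%, 45% or 36.4%, close to the response rates quoted in Background. With d = p(comparator) − p(face-to-face), the interval is d ± 1.96 × √[p₁(1−p₁)/n₁ + p₂(1−p₂)/n₂].

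| Comparator returns | Face-to-face returns | All eligible: difference (95% CI), points | Returners only |
|---|---|---|---|
| 141/202 | 172/202 | -15.3 (-23.4 to -7.3) | 141/141 vs 172/172: 0 |
| 91/202 | 172/202 | -40.1 (-48.5 to -31.7) | 91/91 vs 172/172: 0 |
| 74/202 | 172/202 | -48.5 (-56.8 to -40.3) | 74/74 vs 172/172: 0 |

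The returners-only difference is 0 with zero variance whatever the true rates, so there is nothing to estimate.

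**3. Consenters-only denominator.** The article never names this set, but it is the next most natural reading. All rates are assumed. Return among all randomised = consent × completion given consent. Each cell gives face-to-face, then comparator.

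| Consent | Completion given consent | All randomised | Difference, all randomised | Difference, consenters |
|---|---|---|---|---|
| 60%, 40% | 90%, 90% | 54%, 36% | -18 points | 0 |
| 40%, 60% | 90%, 90% | 36%, 54% | +18 points | 0 |
| 60%, 60% | 95%, 70% | 57%, 42% | -15 points | -25 points |

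The first row hides a deficit of 18/2.5 = 7.2 times the margin. The second hides an advantage. The third makes a deficit look larger. The bias has no fixed direction.

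A difference of 0 among consenters need not pass the margin either. In the first row there are about 121 and 81 consenters, and the half-width is 1.96 × √[0.9 × 0.1 × (1/121 + 1/81)] = 8.4 points. The lower limit of -8.4 lies below -2.5.

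The figure of 202 serves here only as a denominator. Whether it suits a 2.5-point margin is a separate question on which this point does not depend.

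**The case against.** The strongest reply is that the rule is loosely worded but harmless. If return status is known for everyone randomised, a complete-case analysis of return yes/no excludes nobody. The returners-only reading refutes itself, and the closing sentence of the same paragraph makes non-return the thing compared. Study design calls the rate of return the primary outcome, and Discussion says that non-responders provide useful data. The sentence may have been meant for questionnaire answers or for covariates in the adjusted model. The article also condenses a fuller protocol, and it mentions a statistical analysis plan that is not shown.

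Much of this stands. The intent to count non-returners is clear. A reader might infer that the trial will delete its failures, or that a consenters-only analysis is planned, but the article supports neither. A reader might also infer that the rule favours non-inferiority in every comparison; the second and third consent scenarios show otherwise. The 18-point figure comes from chosen rates and is not a forecast.

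What does not stand is that nothing needs correcting. The harmless reading requires missing data to mean something other than non-return, and the paragraph uses it for non-return. The scope that would rescue the sentence is not stated. Nor is this a detail left to the analysis plan: the article names a population, and it is at odds with its own primary outcome.

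**Conclusion.** The point holds as a contradictory rule. In its plain sense, the complete-case sentence is incompatible with the Primary outcome, Sample size and Discussion sections. Followed literally, it leaves the primary comparison inestimable. Followed as consenters-only, it answers a different question, with a bias whose size and sign depend on how consent and completion differ by mode. In the assumed scenarios, the consenter difference departs from the all-randomised difference by 10 to 18 points, against a margin of 2.5.

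This rests on reading missing data as non-return, which the paragraph's last sentence supports, and on illustrative rates for every size quoted. It does not show that the executed analysis would exclude anyone.

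The covariate-adjusted analysis is a secondary matter. An unscoped complete-case rule would also drop randomised people with, say, no admission NIHSS. The article plans to collect these baseline data for everyone randomised and invited and gives no missingness rate, so the loss cannot be sized.

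**What to change.** Replace the complete-case sentence with wording such as:

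> The primary analysis includes every randomised eligible person in the arm allocated. Anyone without a returned method-specific PRHSQ, including non-consenters and non-responders, counts as not returned.

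Then confine complete-case analysis explicitly to questionnaire item data, and use the term missing data only for values that are truly unknown. In the adjusted analysis of the primary outcome, it is preferable to keep people with a missing baseline covariate, for example by a missing category or simple imputation; this is a lesser point.

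The cost is wording only. Every randomised person has a research number against which a return can be recorded, so return status can be established for all, and baseline data are already planned for all. No extra participants or data are needed. The change should be made before unblinding and carried into the statistical analysis plan.
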